### Outcomes

Outcomes data will be collected via self-report, with participants completing an online assessment containing a series of standardized psychometric measures at Baseline, End of Treatment, and 3-month and 6-month follow up timepoints. Additionally, engagement data (time spent accessing the program, number of BCTs engaged with) will be collected automatically via the BFO backend database for those participants in the interventional arm.

The primary outcome will be self-reported substance use compared to baseline following treatment completion, and at three and six-months follow-up, which will be measured using the following questions:Weekly use of primary problem substance (i.e., ‘How many days in the past week did you use [primary substance]?’‘How much [primary substance] did you use each day?’)

Secondary outcomes will be measured at corresponding time points using the following standardized measures:Severity of Dependence Scale (SDS) [37, 38]: A five-item scale measuring severity of substance dependence—internal reliability: α = 0.81–0.90; test–retest reliability ICC = 0.89.Patient Health Questionnaire-4 (PHQ-4) [39]: A four-item scale that measures severity of depression and anxiety—internal reliability, α = 0.81.Five items (1, 2, 17, 18, 20) from the World Health Organization Quality of Life scale (WHOQoL-BREF) [40]—internal reliability of these five items, α = 0.84.Recovery Progression Measure (RPM) [34, 35]: A 36-item scale measuring functioning in six biopsychosocial domains functioning that are implicated in all SUDs and recovery from SUDs—internal consistency, α = 0.89; test–retest reliability, ICC = 0.73.

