### Randomization

Randomization will occur at the level of individual participants using a random allocation sequence via the Research Randomizer [41]. Sequentially numbered opaque sealed envelopes containing the group that each participant will be allocated to will be prepared prior to commencement of the study. Treatment allocation sequences will be generated by a member of the research team and disseminated to the participating organization via sealed opaque envelope. Participants will be enrolled into the study and subsequently assigned to a treatment condition by a member of the research team at the participating organization. Because this study is a non-pharmaceutical study open-label study, no blinding is required—however, the study statistician will be blinded to treatment allocation when analyzing study data. Participants will be identified by a participant identification or randomization number only on all trial documentation, except for informed consent documents. Where there is a need for Sponsor personnel to verify trial documentation against medical records or other data sources containing identifiable information, this will be permitted by the research site, provided that subject confidentiality is maintained in accordance with local regulations and requirements.

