### Data analysis and management

Data will be analyzed using SPSS® Version 26.0 (or later). The principal data analytical strategy will be a repeated measures analysis of variance (ANOVA) in order to make a longitudinal comparison of treatment groups for the primary and secondary outcomes along the follow-up time points. The appropriate 95% confidence interval will be applied. The main statistical analyses will be conducted by the Chief Investigator with specialist statistical support from co-investigators at the collaborating academic institution (University of Manchester). Main analyses based on published research [26] indicate that data will likely be non-normally distributed, and that therefore, the most appropriate analyses will be Kruskall-Wallis ANOVA and Analyses of Covariance (ANCOVA) at each psychometric assessment time point, in order to compare study groups.

Changes over time in psychometric assessment scores within each group will be conducted using Wilcoxon Signed Ranks Tests—a more conservative significance level of p = 0.001 will be adopted to compensate for the increased risk of Type I errors associated with multiple comparisons. Effect sizes will also be calculated to examine robustness of between-group differences and within-group changes, in addition to examining clinically significant changes over time by analyses of numbers of participants fulfilling clinical threshold scores for substance dependence, depression and anxiety. Regression analyses will be conducted to control for baseline differences between groups in terms of sample size, severity of substance dependence and mental health sequelae, psychosocial functioning and quality of life, as measured by the battery of standardized psychometric assessments. Additionally, mixed effects models will be used to compensate for the independence assumption inherent to regression analyses.

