Responsibility for data management will lie with the Chief Investigator, and the Principal Investigator within the Sponsor organization. A detailed allocation of responsibilities will be completed by the Chief Investigator as a separate document (‘Delegation Log’), which will be followed by the investigational site personnel and Sponsor personnel. Routine data monitoring for this trial will be completed by the Sponsor Clinical Trial Coordinator, who will conduct monitoring visits on a pre-determined schedule with the site Principal Investigator, other relevant clinicians at site, and trial staff. The Clinical Trial Coordinator will report directly to the Chief Investigator and Sponsor organization. Monitoring and auditing intervals for this study will be based on a risk-assessment undertaken by the Sponsor prior to first participant recruitment and will be appropriately communicated to the study site in advance. The trial will adhere to any routine internal audit processes already in place within the participating organization.

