## Discussion

This protocol describes the methodology for an RCT to examine the effectiveness of digital CBT for SUD—Breaking Free Online (BFO)—and fortnightly recovery check-in phone calls, when delivered as an adjunct to standard treatment, compared with standard treatment only, at an NHS Mental Health Trust in North-West England. This design could be interpreted as a limitation as it does not allow direct effectiveness comparisons to be made between digital treatment and in-person treatment. However, this design has been selected in order to enhance ecological validity of the study, as it most accurately reflects how BFO is delivered in treatment services, i.e., as an adjunct to standard treatments and not as a replacement.

Another limitation of the methodology is that it will not be possible for the investigators and practitioners to be blinded to the allocation of participants, which could potentially bias outcomes—however, the study statistician will be blinded to treatment allocation. Additionally, because the level of randomization will be at the level of individual service users, this may pose a risk of contamination across the two study groups if individual participants have an opportunity to interact with one another. Participants may also join the study at different points in their treatment and recovery journey—therefore a ‘floor effect’ could occur that may under-estimate the effectiveness of BFO if a proportion of participants start at a baseline of abstinence/low substance use and therefore relatively good psychosocial functioning.

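### The promised blinding of the study statistician does not cover the Chief Investigator, to whom the main analyses are assigned

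*Protocol article*

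**What the plan says.** Four places in the protocol article bear on who analyses the data and what that person knows.

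- **Randomization.** The trial is declared open-label: "Because this study is a non-pharmaceutical study open-label study, no blinding is required". The same sentence then makes one exception: "the study statistician will be blinded to treatment allocation when analyzing study data".
- **Discussion, limitations.** The article concedes that "it will not be possible for the investigators and practitioners to be blinded to the allocation of participants", accepts that this could bias outcomes, and sets against it that "the study statistician will be blinded to treatment allocation".
- **Data analysis and management.** On who does the work: "The main statistical analyses will be conducted by the Chief Investigator with specialist statistical support from co-investigators at the collaborating academic institution". No study statistician is mentioned there. On the data: "Responsibility for data management will lie with the Chief Investigator, and the Principal Investigator within the Sponsor organization".
- **Outcomes.** Outcomes are self-reported. Engagement data (time in the program and number of techniques used) "will be collected automatically via the BFO backend database for those participants in the interventional arm".

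**The concern.** The article recognises a source of bias and names a measure to offset it. That measure works only if the blinded person is the one who makes the analytic decisions. Here those decisions appear to be given to a member of the group described as impossible to blind.

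The stakes come from three features of the trial. Treatment is open-label. The primary outcome is the participant's own report of substance use, so bias in the outcome itself cannot be excluded and the analysis stage is where blinding can still be kept. And the analysis section leaves room for choice: it calls repeated measures ANOVA the principal strategy, then describes Kruskal-Wallis and ANCOVA at each time point as the most appropriate because the data are likely to be non-normal. An analyst who knows the arms and has to settle such a choice can favour one result without intending to.

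**Working it through.** There is no figure to reproduce. The question is whether the statements about roles can all hold, so they are set side by side.

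1. *Who is promised to be blinded?* The study statistician, when analysing the data (Randomization; repeated in the Discussion).
2. *Who is said not to be blindable?* The investigators and practitioners (Discussion). No role is exempted.
3. *Who conducts the main analyses?* The Chief Investigator, with co-investigators giving statistical support (Data analysis and management).
4. *Is the Chief Investigator shielded from allocation anywhere?* No. The article describes no masked arm codes for the role, and it gives the role shared responsibility for data management.
5. *Would hiding the arm label be enough?* Not by itself. BFO engagement data exist only for the intervention arm, so any file containing them shows who was allocated to BFO.

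The possible ways of reconciling items 1 to 3 are these:

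| Reading | Consequence |
|---|---|
| The study statistician is a separate person | The blinded person is not the one assigned the main analyses |
| The study statistician is one of the supporting co-investigators | The blinded person only supports. A co-investigator also falls under the investigators who cannot be blinded |
| The Chief Investigator is the study statistician | Items 1 and 2 contradict each other directly |
| Investigators means site staff only, and the Chief Investigator works on masked data | The statements would agree, but nothing in the article says this |

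Under the first three readings the safeguard fails to cover the main analyst or contradicts itself. The fourth would rescue it, but only with provisions that are not in the text.

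**The case against.** The best case for the plan is that the Discussion never names the Chief Investigator. Data analysis and management distinguishes that role from the site Principal Investigator, so the unblinded investigators could be the site team. The same section leaves detailed responsibilities to a separate delegation log, and the article is a condensed protocol. This lowers certainty about the Chief Investigator's actual status, and for that reason the point rests on the plain reading and not on an explicit statement. It does not remove the conflict: the article positively assigns the main analyses, and a log that assigned them elsewhere would contradict it.

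A reader might also infer several stronger things that the document does not support.

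- *That blinded analysis is the only protection against bias.* It is not. Allocation uses sequentially numbered opaque sealed envelopes, and the analysis follows intention to treat. Blinded analysis is the only counterweight that the Discussion sets against unblinded investigators, which is narrower.
- *That a published claim of blinded analysis would be false.* The promise concerns the study statistician and could be literally true of someone in a supporting role. The fair criticism is that it does not extend to the assigned main analyst.
- *That monitoring feeds arm-level results to the Chief Investigator.* The article says only that "The Clinical Trial Coordinator will report directly to the Chief Investigator and Sponsor organization". Nothing shows that comparative data travel along that line.
- *That interim results will reach the person leading the trial.* The article does not say who runs the interim analysis. A condensed article may leave that to the full protocol or analysis plan, so it is no finding here.
- *That analyst freedom can be counted as methods multiplied by tests, or that covariates are chosen from the data.* The named methods have different roles, and the covariate domains are listed in advance. Neither claim is established.

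**Conclusion.** The point holds: the statements on blinding and the assignment of the main analyses do not agree, and the stated safeguard does not cover the person who is to run those analyses. The gap extends to all the main comparisons, because the assignment is made for the main analyses as a whole. The effect on the results cannot be quantified from the document, and no direction or size of bias is claimed.

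The conclusion rests on two assumptions: that the Chief Investigator belongs to the investigators whom the Discussion describes as unblinded, and that no masking arrangement exists for that role beyond what the article states. Even if the first assumption were wrong, the article would still need to say who analyses blinded and how. The matter should be corrected, but it does not invalidate the design.

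**What to change.** Amend Data analysis and management so that the blinded study statistician referred to in Randomization and the Discussion conducts the primary intention-to-treat analysis, as follows:

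- The analysis file carries arms coded A/B, and the BFO engagement variables are withheld.
- The arm code and engagement data are released only after the primary output is signed off.
- The Chief Investigator interprets the results after unmasking.
- Per-protocol and engagement analyses are run after that, since they need intervention data that reveal the arm.

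The article does not give the study statistician's affiliation, and the university is described only as providing supporting co-investigators. The amendment should therefore state which role is meant and confirm that its holder has no access to allocation.

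If this cannot be arranged, withdraw the blinding statements from Randomization and the Discussion, and let the limitation stand without that counterweight.

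The cost is a coded data export and re-allocation of the task within the existing team, provided that the statistician the protocol already refers to is available to do the work.

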### Participants

Participants will be service users currently in treatment for SUD who meet the following inclusion criteria: (i) aged 18 years or above, (ii) experiencing problem alcohol and/or drug use for ≥ 12 months requiring treatment, as determined by clinical personnel at the service, (iii) willing to comply with an eight-week treatment program for problem alcohol and/or drug use, (iv) willing to provide outcome measures post-treatment, and at three and six-months follow-up, (v) able to read, write and communicate in the English language, (vi) willing and able to access an internet enabled device for the eight-week treatment period, (vii) willing and able to give informed consent for participation in the study, and capable of understanding and complying with protocol requirements.

Exclusion criteria are as follows: (i) under 18 years of age, (ii) participation in any other alcohol and/or drug related clinical studies within 12 months prior to date of consent, (iii) detention under the Mental Health Act, (iv) clinically significant intellectual or developmental disability which may impair ability to engage with BFO and/or complete the necessary assessment measures included in the methodology, (v) pregnancy (as self-reported), (vi) previous use of BFO to address drug or alcohol use within the past 12-months.

The projected sample size will require 61 evaluable participants in each of the two treatment groups (interventional and control) to achieve enough observed power (assuming an observed power of 0.80 with α = 0.05) with an allowance of 50% attrition at three and six-months follow-up, in order to detect a medium effect size (d ≤ 0.50). Therefore, to obtain a total of 122 evaluable participants, it is estimated that a total of 183 participants will need to be recruited and screened. These estimations have been based on previous alcohol and drug studies size samples [8], some of which have used longitudinal statistical analyses.

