Interim analyses will be performed on the first 30 participants of each group to have completed the three- and six-months follow-up assessments after treatment completion. The data will be subjected to ANOVA and ANCOVA. Changes over time in psychometric assessment scores within each group will be conducted using Wilcoxon Signed Ranks Tests, assuming data are non-normally distributed. If following the interim analysis, a significant difference in outcomes is detected between the groups, either the sample size will be recalculated or recruitment will be discontinued, depending on the statistical power obtained.

Sub-group analyses will be conducted to examine the influence of sociodemographic variables such as age and gender, and clinical characteristics such as primary problem substance and clinically relevant depression and anxiety, on outcomes. Sub-group analyses will be conducted using ANOVA, ANCOVA and regression.

Intention-to-treat (ITT) principles will be followed, with data from all randomised participants being included in these analyses. Mixed effect models will be used to handle missing data by maximum likelihood estimation, which uses all available data from randomised participants and has been demonstrated to minimise bias more effectively than other approaches [46]. A number of strategies will be employed to maximize follow-up and prevent missing data as far as possible. These will include the study team contacting participants directly to chase-up incomplete assessments and working closely with clinical staff to contact those participants who cannot be contacted by the study team directly—reasons for missing data and drop-out will be recorded where this information is available. Additionally, non-randomised, observational, per-protocol comparative analyses will be conducted using data only from participants who fulfilled all protocol requirements in terms of eligibility, intervention receipt, and outcome assessment completion, in order to ascertain effects from BFO under ideal conditions.

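### ANCOVA is justified by non-normality and paired, unranked, with a Kruskal-Wallis test that cannot adjust for baseline, while the interim names ANOVA and ANCOVA

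*Protocol article*

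**What the plan says.** All references are to the protocol article.

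- **Outcomes.** "The primary outcome will be self-reported substance use compared to baseline following treatment completion, and at three and six-months follow-up". It is measured by two items: days of use of the primary substance in the past week, and amount used per day.
- **Data analysis and management, first paragraph.** Repeated measures ANOVA is the principal strategy for primary and secondary outcomes. The next sentence reads "The appropriate 95% confidence interval will be applied". The paragraph then says that "data will likely be non-normally distributed, and that therefore, the most appropriate analyses will be Kruskall-Wallis ANOVA and Analyses of Covariance (ANCOVA"), applied at each time point to compare the groups.
- **Same section, second paragraph.** Effect sizes, regression that controls for baseline differences, and mixed effects models are added.
- **Same section, interim analyses.** On the first 30 completers per group, "The data will be subjected to ANOVA and ANCOVA". The next sentence plans within-group tests "using Wilcoxon Signed Ranks Tests, assuming data are non-normally distributed". A significant group difference leads either to a new sample size or to the end of recruitment.
- **Same section, intention-to-treat.** Mixed effects models fitted by maximum likelihood handle missing data.
- **Participants.** The sample size is "61 evaluable participants in each of the two treatment groups", "assuming an observed power of 0.80 with α = 0.05", "in order to detect a medium effect size (d ≤ 0.50").

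**The concern.** Three statements do not fit together.

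First, the inference is wrong. ANCOVA rests on normally distributed errors, as does the ANOVA it is brought in to replace. Its merit is baseline adjustment, which is a good reason to use it, but not the one given.

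Second, Kruskal-Wallis takes no covariate. It cannot adjust for baseline, although the primary outcome is defined relative to baseline, and by itself it yields a p-value without an effect in days or amount.

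Third, the article calls one analysis principal and two others most appropriate, adds regression and mixed models, and uses a differently worded set of tests at the interim. It does not say which result decides when they differ.

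At stake are some power, and a verdict that may depend on which of two named tests is read.

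**Working it through.** **1. The plan's own figure.** Inputs: d = 0.50, α = 0.05, power 0.80 (Participants). Sidedness is not stated; two-sided is assumed.

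n per arm = 2 × (1.960 + 0.842)² / 0.50² = 62.8, so 63. The exact t-test gives 64 and the one-sided formula gives 50. The stated 61 is close to the two-sided result; power at 61 is 0.789. This is the power of an unadjusted comparison of two means.

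**2. What baseline adjustment is worth with normal data.** The baseline-to-follow-up correlation ρ is not in the article, so it is varied. ANCOVA reduces the SD by √(1 − ρ²). A change score has SD √(2(1 − ρ)). Kruskal-Wallis has relative efficiency 0.955, so 61 per arm acts like 61 × 0.955 = 58.3. Power at 61 per arm, d = 0.50:

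| ρ | Kruskal-Wallis | Change score | ANCOVA |
|---|---|---|---|
| 0.3 | 0.77 | 0.646 | 0.825 |
| 0.5 | 0.77 | 0.789 | 0.890 |
| 0.7 | 0.77 | 0.946 | 0.972 |

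**3. A 0–7 day outcome, four effect patterns.** Simulation of one follow-up time point, 1,500 trials per setting, latent ρ = 0.5, effects of d 0.36–0.45, two-sided 0.05. Shapes, ρ and effects are assumptions. The smaller size is what remains if 183 are recruited and 50% are lost: 183 × 0.5 / 2 = 45.75, about 46 per arm. Power in %; PO is a proportional-odds model with baseline days:

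| Pattern | KW, 46 | ANCOVA, 46 | PO, 46 | PO − KW, 46 | KW, 61 | PO, 61 | PO − KW, 61 |
|---|---|---|---|---|---|---|---|
| U-shaped | 58 | 62 | 65 | 7 | 68 | 77 | 9 |
| Floor-heavy | 50 | 52 | 59 | 9 | 63 | 70 | 7 |
| Effect on abstinence only | 47 | 44 | 56 | 9 | 63 | 70 | 7 |
| Effect among users only | 29 | 63 | 40 | 11 | 39 | 51 | 12 |

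Type I error of the PO model was 4–6%. A separate simulation at ρ = 0.5 and both sample sizes put Kruskal-Wallis 5–11 points below its baseline-adjusted rank counterpart in all four patterns, and lower still on change scores. Together these give the range of 5–12 points.

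**4. Other shapes and correlations.** A further simulation used 61 per arm, 3,000 trials per setting and a shift of 0.5 on the latent scale (on the log scale for the log-normal ratio):

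| Shape | ρ | KW | ANCOVA | Rank ANCOVA | KW and ANCOVA disagree |
|---|---|---|---|---|---|
| Normal | 0.5 | 0.756 | 0.879 | 0.857 | 0.159 |
| 0–7 days | 0.3 | 0.709 | 0.721 | 0.734 | 0.098 |
| 0–7 days | 0.5 | 0.688 | 0.750 | 0.768 | 0.140 |
| 0–7 days | 0.7 | 0.698 | 0.850 | 0.876 | 0.204 |
| Log-normal ratio | 0.3 | 0.768 | 0.609 | 0.794 | 0.255 |
| Log-normal ratio | 0.7 | 0.756 | 0.772 | 0.951 | 0.255 |

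For 0–7 days the gap between rank ANCOVA and Kruskal-Wallis is 2.5, 8.0 and 17.8 points at ρ = 0.3, 0.5 and 0.7, so its size depends on ρ.

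**5. Two unranked tests.** At ρ = 0.5 with 0–7 days and a real effect, Kruskal-Wallis and ANCOVA gave different verdicts in 15–38% of trials in the simulation of step 3, 14% in step 4, and 12–20% in the separate simulation. With no effect, at least one was significant in 6–8%, 6.7% and 6.5–8% respectively, against a nominal 5%.

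**6. Validity of ANCOVA.** With no effect, the type I error of raw-scale ANCOVA at 61 per arm was 0.040–0.053 across every shape and ρ tried.

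**The case against.** The strongest reply is that baseline-adjusted ANCOVA is already planned, so little is lost. Over the four patterns at 46 per arm, ANCOVA averages (62 + 52 + 44 + 63) / 4 = 55.25% and proportional odds (65 + 59 + 56 + 40) / 4 = 55.0%. This stands. It rules out presenting the ordinal model as generally better than ANCOVA, but it does not settle which of the planned tests decides.

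Several stronger readings are tempting, and the documents do not support them:

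- *ANCOVA is invalid for these data.* Its assumption concerns the errors, and its type I error held. Non-normality can cost it power.
- *Kruskal-Wallis always loses power.* Against raw-scale ANCOVA it can win under strong skew (0.768 against 0.609 for the log-normal ratio at ρ = 0.3). The loss is against a baseline-adjusted method suited to the distribution.
- *The interim drops baseline adjustment.* ANCOVA is named at both looks. The word ANOVA there may even be short for Kruskal-Wallis ANOVA, but a step that can end recruitment should not rest on that guess.
- *No confidence interval is possible.* The promise of a 95% CI follows the repeated measures ANOVA sentence, and effect sizes, regression and mixed models are also planned.
- *A floor is expected.* The Discussion says only that one could occur.

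The article also does not say whether Kruskal-Wallis is run on raw or change scores. Change scores would use the baseline, but simulated power was then lower still.

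**Conclusion.** The point holds as an error of reasoning and an unresolved choice between tests. Non-normality does not support ANCOVA. Unadjusted Kruskal-Wallis is a poor match to an outcome defined against baseline. The final and interim analyses name different, unranked sets of tests.

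The size is moderate: about 5–12 points of power for Kruskal-Wallis against an adjusted rank or ordinal analysis, disagreement with ANCOVA in roughly 12–38% of trials with a real effect, and a 1–3 point excess of false positives if either test may be read as the result. These figures rest on assumed outcome shapes, a 0–7 day scale, a correlation of 0.5 and a single follow-up time point. Amount per day was not modelled from trial information. A different correlation moves the power gap, as step 4 shows. The wording should be changed, but the planned ANCOVA need not be abandoned.

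**What to change.** - Name one baseline-adjusted model as decisive for the between-group comparison of the primary outcome. Place it within the mixed effects model already planned, with the baseline value as covariate.
- Report its adjusted group difference with a 95% CI, by bootstrap or robust standard errors in view of the expected distribution.
- Use the same model at the interim and the final analysis.
- Delete non-normality as the reason for ANCOVA; baseline adjustment is the reason.
- Replace unadjusted Kruskal-Wallis by a baseline-adjusted rank or proportional-odds analysis as the named sensitivity analysis, for both days used and amount per day. Proportional odds is an option, not a required replacement for ANCOVA: it had 40% power against 63% when only users' days changed.

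The cost is analysis wording, settled before any comparison by group, and some programming for the interval. No extra data or participants are needed. The small downside is that the unadjusted rank test, which can beat raw-scale ANCOVA under strong skew, no longer decides; the adjusted rank sensitivity analysis keeps that information in view.

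### The only covariate list the protocol names includes sample size and leaves out baseline use of the primary substance, the baseline of the primary outcome

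*Protocol article*

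**What the plan says.** The Data analysis and management section of the protocol article sets out several between-group analyses:

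- The principal strategy is repeated measures ANOVA across the follow-up points.
- Because non-normal data are expected, Kruskal-Wallis tests and ANCOVA are then described as most suitable at each time point. No ANCOVA covariates are named.
- A supporting regression has a named list: "Regression analyses will be conducted to control for baseline differences between groups in terms of sample size, severity of substance dependence", followed by mental health, psychosocial functioning and quality of life, all as measured by the psychometric battery.
- Mixed effects models are also planned, including for missing data.

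Primary substance appears in the same section only as a sub-group factor, among "clinical characteristics such as primary problem substance".

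The Outcomes section defines the primary outcome as self-reported use of the primary substance (days in the past week, and amount per day), compared with baseline. The secondary outcomes are the SDS, PHQ-4, five WHOQoL-BREF items and the RPM. The Discussion anticipates a floor effect "if a proportion of participants start at a baseline of abstinence/low substance use".

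**The concern.** The regression sentence has three faults.

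1. **Sample size is not a covariate.** It is a property of the trial or the arm and takes no participant-level value. No analysis plan could carry out the sentence as written.
2. **The primary outcome's own baseline is missing.** Every secondary outcome has its baseline in the list, and the primary outcome does not. Earlier use is a natural candidate to predict later use. Primary substance is also absent, although the outcome questions are worded around it and amounts of different substances are not in common units.
3. **The purpose is misdescribed.** Baseline differences between randomised arms are due to chance. The reason to adjust is that a variable predicts the outcome, whether or not the arms happen to differ on it.

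At stake is precision for the primary comparison, in a trial that expects heavy attrition. A covariate set fixed in advance would also leave no argument later about which adjusted result counts.

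**Working it through.** **Reading the list against the outcomes**

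| Term in the regression list | Matching measure in Outcomes |
|---|---|
| Sample size | none; not a participant variable |
| Severity of dependence | SDS (secondary) |
| Mental health | PHQ-4 (secondary) |
| Psychosocial functioning | RPM (secondary) |
| Quality of life | WHOQoL-BREF items (secondary) |
| Not listed | days and amount of primary-substance use (primary) |

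**The plan's own figure**

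The Participants section gives these inputs:

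- "assuming an observed power of 0.80 with α = 0.05"
- "in order to detect a medium effect size (d ≤ 0.50", read here as d = 0.50
- "The projected sample size will require 61 evaluable participants in each of the two treatment groups"

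Sidedness is not stated, so two-sided is assumed. On the standardised scale (SD = 1):

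n per arm = 2 × (1.960 + 0.842)² / 0.50² = 62.8, so 63. The stated 61 is within two participants of this.

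Power at 61 per arm = Φ(0.50 × √(61/2) − 1.960) = Φ(2.761 − 1.960) = 0.789. The t-test version gives 0.782. Both are close to the stated 0.80, and neither involves a covariate.

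**Adding baseline use as a covariate**

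Let r be the correlation between baseline and follow-up use. The documents give no value, so r is an assumption. Adjustment reduces the residual SD to √(1 − r²), and power = Φ(2.761 / √(1 − r²) − 1.960). At r = 0.5: 2.761 / 0.866 = 3.188, less 1.960 is 1.228, and Φ(1.228) = 0.890.

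For comparison, a simple change score has SD √(2(1 − r)), and power = Φ(2.761 / √(2(1 − r)) − 1.960).

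| Assumed r | Residual SD | Power, baseline as covariate | n per arm for 0.80 | Power, change score |
|---|---|---|---|---|
| no adjustment | 1.000 | 0.789 | 63 | – |
| 0.2 | 0.980 | 0.805 | 61 | 0.588 |
| 0.3 | 0.954 | 0.825 | 58 | 0.646 |
| 0.5 | 0.866 | 0.890 | 48 | 0.789 |
| 0.7 | 0.714 | 0.972 | 33 | 0.946 |

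Against an unadjusted test the gain is about 2, 4, 10 and 18 points. Subtracting baseline is not a substitute for adjusting for it: the change score has lower power at every r shown.

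**Gain over a model that already holds a listed covariate**

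As an illustration, assume that dependence severity correlates 0.3 with the outcome and 0.4 with baseline use. Dependence alone then gives power 0.825 at 61 per arm. With both covariates, R² = (0.3² + r² − 2 × 0.3 × r × 0.4) / (1 − 0.4²).

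- r = 0.3: R² = 0.129, power 0.841, a gain of about 2 points.
- r = 0.5: R² = 0.262, power 0.895, a gain of 7 points.

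If baseline use is already a covariate, there is nothing further to gain. All figures rest on normal theory at a single time point, whereas the protocol expects non-normal data, so they indicate scale only.

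**The case against.** The strongest reply is that this is one sentence about a supporting analysis. ANCOVA is planned at each time point, and the baseline of the outcome is its usual covariate. Repeated measures ANOVA and mixed models may carry baseline as a time level, and the primary outcome is itself defined relative to baseline. A condensed article may properly leave ANCOVA covariates to the analysis plan. All of this stands. A reader might infer that the trial will lose power. The document does not show that, because absence from the regression list is not absence from every model.

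Three other inferences also go too far:

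- **That covariates will be picked by observed imbalance.** The protocol gives a list in advance and describes no imbalance test or selection rule. The phrasing is loose, but it is not a data-driven procedure.
- **That the listed terms are the wrong ones.** Apart from sample size they are plausible prognostic factors. The Introduction itself reports that baseline clinical characteristics are associated with outcomes.
- **That primary substance is ignored.** It is examined in the sub-group analyses. It is missing only from the adjustment list.

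The expected floor effect gives limited support. It shows that wide spread in baseline use is foreseen, but adjustment does not create room to improve in people already abstinent.

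None of this repairs the sentence itself. Sample size remains an error, and the one list that is spelled out omits the primary outcome's baseline. Nor does the planned Kruskal-Wallis test fill the gap, since it takes no covariates.

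**Conclusion.** The point holds as a correction to the named covariate list and to the stated purpose of adjustment. The inclusion of sample size is a plain error. The omission of baseline primary-substance use is a visible gap, because every secondary measure's baseline is covered. Neither invalidates the trial.

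The possible benefit runs from about 2 points of power (r = 0.2) to 18 points (r = 0.7) against an unadjusted two-sample test at 61 per arm. That range assumes d = 0.50, two-sided 5% significance and approximately normal residuals. The unadjusted test is a benchmark and not the protocol's principal analysis. Where the listed scores are already fitted the gain is smaller, and where baseline use is already a covariate it is nil. For a mixed model that carries baseline as a time level, what remains to be gained depends on how the group contrast is set up, which the article does not say.

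**What to change.** 1. Delete sample size from the regression sentence.
2. State that the between-group models that take covariates (ANCOVA, regression, and mixed models where baseline is not already a time level) adjust for the baseline value of the outcome analysed. For the primary outcome this is baseline use of the primary substance.
3. Add primary problem substance as a covariate, in categories that the sponsor sets beforehand, with a rule for merging sparse ones.
4. Replace the reference to controlling for group differences with a statement that the covariates are prognostic and fixed in advance, whatever imbalance is observed. Dependence, mental health, functioning and quality of life can stay as further prespecified terms.

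The cost is wording only, since both added variables are already collected. The change should be dated before any comparison by arm, including the planned interim analysis of the first 30 participants per group.
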